##### Analysis of secondary endpoints

Secondary endpoints will be described using the mean and standard deviation for continuous variables and percentages for qualitative variables. The rate of missing data at each HRQoL measurement time will be reported. HRQoL results within treatment groups and in all evaluable patients will be assessed using descriptive statistics. The adverse events occurring during the study, according to the NCI CTCAE V4, will be reported by group. There will be no comparative analysis between the sunitinib and pazopanib groups. Survival outcome (OS, PFS, TTD) will be estimated using the Kaplan–Meier method. Median survival will be described with confidence intervals (one-sided statistical test for significance (α: 5%)) in each of the treatment groups and in all evaluable patients.

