#### Key trial objectives

The primary objective of the QUANARIE study is to evaluate the proportion of patients having good compliance with REMOQOL during the first 12 months of treatment.

The key secondary objectives are the following:To report the number of patients to whom the study was proposed divided by the number of patients initiating sunitinib or pazopanib treatment in each centre;To report the number of patients who agreed to participate in this study as compared with the number of refusals divided by the total number, by centre and by molecule type (sunitinib or pazopanib);To estimate the rate of missing data defined as the numbers of completely or partially filled items by HRQoL questionnaire and for each measurement time. We will consider a questionnaire as filled out if at least 10 items are completed;To Describe the toxicities collected by the physician according to the NCI CTCAE V4 and reported by the patient according to the eight symptomatic dimensions of the QLC-C30 questionnaire and the six supplementary symptomatic dimensions;To evaluate Physicians’ satisfaction regarding the CHES software and REMOQOL by a questionnaire submitted at the end of the inclusion.

The exploratory objectives are the following:To estimate OS, defined as the time from the start of treatment to death;To estimate PFS, defined as the time from the start of treatment to progression or death;To estimate Time to deterioration of HRQoL (TTD): TTD will be defined as the time from the start of treatment to the first significant deterioration (either increase or decrease depending of the scale) in a HRQoL score as compared with the baseline score with no further significant improvement as compared to the baseline score, or death [29, 30]. Pre-specified targeted HRQoL dimensions will be global quality of life (QL), physical functioning (PF), and fatigue (FA). In these dimensions, will be considered as significant a deterioration over time of ten points at least and an improvement of eight points in QL, seven points in PF and nine points in FA [31].

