#### Population analysis

Evaluable patients will be defined as all patients who filled out at least one questionnaire and are still alive or without progressive disease three months after the start of treatment.

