## Discussion

A better understanding of the pathogenesis of metastatic clear-cell renal-cell carcinoma has made it possible for the development of novel therapeutics capable of changing patient management [34]. Some tyrosine kinase receptors and their ligands have been shown to play an important role in tumour growth and angiogenesis. Inhibition of VEGF signalling through the use of antibodies or VEGF antagonists has demonstrated potent antitumour activity in the mRCC setting [35]. To date, nine targeted therapies have been approved by regulatory authorities in the United States and Europe, which have revolutionised the treatment of mRCC and largely contributed to what can be called the chronic care of this disease. As an example, in an unselected “real-life” cohort of 224 metastatic patients, the median OS for patients with a good prognosis, according to the Heng prognostic score [36], was 32 months [34]. This allowed expansion of the number of treatment options and sequences in this setting. Moreover, new generation immunotherapy has recently been approved by the FDA for a first-line setting [37].

From the patient’s perspective, it is essential that this improvement in the duration of survival is not at the cost of high toxicity; therefore, improvement of TKI tolerance has become a major topic of research in the mRCC field. For instance, the PISCES study evaluated patient preference of sunitinib or pazopanib [5]. Some trials have evaluated alternative administration schedules of sunitinib to improve its tolerability [38, 39]. In daily clinical care, the management of side effects related to TKI is an important part of mRCC patient care to enhance treatment compliance. A German group highlighted the fact that the benefit of these drugs may differ in routine practice as compared with patients included in clinical trials [40]. In parallel, there is increasing evidence that PRO in routine care may help in the management of sides effects [15, 16].

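### Pooled OS, PFS and TTD medians count from treatment start in a set selected on 3-month status, and carry a one-sided test that has no hypothesis

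*Protocol article*

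**What the plan says.** The relevant statements stand in three sections of the protocol article.

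- **Key trial objectives.** Under the lead-in "The exploratory objectives are the following", all three time-to-event outcomes start at treatment initiation: "To estimate OS, defined as the time from the start of treatment to death"; "To estimate PFS, defined as the time from the start of treatment to progression or death"; and "TTD will be defined as the time from the start of treatment to the first significant deterioration" in an HRQoL score, "with no further significant improvement as compared to the baseline score, or death".
- **Population analysis.** Evaluable patients need at least one completed questionnaire and must be among those who "are still alive or without progressive disease three months after the start of treatment".
- **Analysis of secondary endpoints.** The three outcomes are estimated by Kaplan–Meier. The medians are described with confidence intervals, followed by the parenthesis and populations "one-sided statistical test for significance (α: 5%)) in each of the treatment groups and in all evaluable patients". The same paragraph rules out any comparison of sunitinib with pazopanib.

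The article states no landmark origin, delayed entry or all-included analysis set for these outcomes. The only hypotheses it gives, under Sample size, concern the proportion of patients with good compliance (60% against 80%).

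**The concern.** Whether a patient belongs to the pooled analysis set depends on what happened in the first three months, yet those months are counted as follow-up. Patients with certain early events are left out, and those who remain contribute event-free time that the selection guaranteed. This is guarantee-time (immortal-time) bias. The reported OS and PFS would look better than the experience of the patients who started treatment.

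The sidedness label is a second, independent problem. A significance test needs a null value or a comparator, and none exists for OS, PFS or TTD. The label also leaves the interval undefined, since a reader could compute it in three ways.

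**Working it through.** **1. The plan's own figures.** The article gives no expected median or null value for OS, PFS or TTD, so there is no survival figure to reproduce. Its one-sided 5% level belongs to the compliance design. With 45 evaluable patients and success at 33 or more, the exact binomial gives a type I error of 0.0446 at 60% and power of 0.9005 at 80%, in line with the planned 0.05 and 0.90. That design is sound, but it supplies no hypothesis for survival.

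**2. Assumptions.** Survival is exponential. PFS medians of 6–12 months and OS medians of 20–32 months are assumptions. The 32-month value appears in the Discussion, but for good-prognosis patients of another cohort, so it serves here only as the upper end of a range.

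**3. OS, if every death before month 3 is excluded.** For t ≥ 3, the estimated curve is S(t)/S(3), with S(t) = 0.5^(t/m). Setting this to 0.5 gives t = m + 3.
- m = 32: S(3) = 0.937, so 6.3% are removed. The median becomes 35 (+9%), and 12-month OS becomes 82.3% instead of 77.1%.
- m = 24: the median becomes 27 (+12%).

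This is an upper limit. Read literally, *or* could keep a patient who died before month 3 without progression. If only half of the early deaths were excluded at m = 32, the divisor would be 1 − 0.5 × 0.063 = 0.9685, and the shift −32 × log2(0.9685) ≈ 1.5 months.

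**4. PFS under the literal *or*.** A living patient who progressed before month 3 stays evaluable, and that event is counted. At most, early deaths are removed. For t ≥ 3 the curve is S_PFS(t)/S_OS(3), and its median is m_PFS × (1 + 3/m_OS).

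| PFS median (assumed) | OS median (assumed) | Estimated PFS median | Shift (months) |
|---|---|---|---|
| 8 | 20 | 9.20 | 1.20 |
| 8 | 32 | 8.75 | 0.75 |
| 10 | 24 | 11.25 | 1.25 |
| 10 | 32 | 10.94 | 0.94 |
| 12 | 32 | 13.12 | 1.12 |

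The least favourable corner of this range, PFS 12 with OS 20, gives 12 × 3/20 = 1.8 months. For PFS 10 with OS 32, 12-month PFS goes from 43.5% to 0.435/0.937 = 46.4%.

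**5. PFS if *and* was meant.** The formula of step 3 applies. A median of 10 months becomes 13, with 1 − 0.5^(3/10) = 18.8% of patients removed and 12-month PFS of 53.6% instead of 43.5%. Medians of 6, 8 and 12 become 9, 11 and 15.

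**6. TTD.** Evaluability does not depend on HRQoL scores, so a deterioration in month 1 or 2 can still be counted. Only the death component is protected by the selection.

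**7. Interval.** A one-sided 5% label fits a single 95% bound (z = 1.645) or a two-sided 90% interval (the same z in each tail). Confidence intervals in the plural, with no level stated, may equally be taken as two-sided 95% (z = 1.960). The text does not settle which is meant.

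**The case against.** Four points on the other side have weight.

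- **The selection rule is *or*, not *and*.** A reader might infer that every PFS event before month 3 is removed, giving the 3-month shift of step 5. No section states an *and* rule, so those figures are only a conditional upper limit. This objection stands.
- **The early deaths may be few.** The eligibility criteria ask for a life expectancy above three months, which the exponential model ignores. If fewer patients die before month 3, the OS shift is smaller. This stands too.
- **The outcomes are exploratory and descriptive.** No decision rests on them and the drugs are not compared, so there is no biased contrast. Nor does the text say outright that the per-drug medians are restricted to evaluable patients; it says so only for the pooled ones. This limits the importance of the point, not the direction of the bias.
- **The parenthesis may be only a confidence-level label** carried over from the compliance design. That is plausible, but it still does not say which interval will be reported, and the words describe a test.

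A reader might also infer that the median OS cannot be estimated, because monitoring lasts two years and the Discussion says "the median OS for patients with a good prognosis, according to the Heng prognostic score [36], was 32 months". At that median, 24-month survival would be 0.5^(24/32) = 59%. The documents do not support this as a criticism. The figure describes a good-prognosis subgroup of an external cohort, the listed eligibility criteria do not restrict entry to good prognosis, and an unreached median is an ordinary, reportable result.

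The unseen analysis plan could add detail, but the article itself already fixes the time origin, the selection rule and the pooled population, and these three do not fit together.

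**Conclusion.** The concern holds for the pooled exploratory curves. Followed as written, the plan gives upward-biased estimates, unequally across the outcomes:

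- **OS:** strongest, up to 3 months on an exponential median if all deaths before month 3 are excluded, and less if patients who die without progression count as evaluable.
- **PFS:** partial, about 1 month under the literal *or* with the assumed medians, and up to 3 months only if *and* was intended.
- **TTD:** through deaths only.

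The sizes rest on exponential survival and assumed medians; the direction does not. The one-sided test wording is a separate defect that stands however the population is read. Neither problem reaches the primary compliance decision by this route.

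**What to change.** 1. Estimate OS, PFS and TTD in all included patients who started sunitinib or pazopanib, from treatment start. Alternatively, declare a month-3 landmark analysis, with the clock starting at month 3 and the results labelled as conditional. Name the same set for the per-drug and the pooled estimates.
2. Delete the one-sided test wording and report two-sided 95% confidence intervals for the medians. Adding 12- and 24-month rates with intervals would help if a median is not reached, but that is optional.

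**Cost:** a change of wording. Table 1 already schedules survival status and progression, so no extra data collection is planned for. The descriptive survival figures will be slightly less favourable, and two-sided 95% limits lie further from the estimate than limits at a one-sided 5% level (z = 1.960 against 1.645).

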## Discussion

A better understanding of the pathogenesis of metastatic clear-cell renal-cell carcinoma has made it possible for the development of novel therapeutics capable of changing patient management [34]. Some tyrosine kinase receptors and their ligands have been shown to play an important role in tumour growth and angiogenesis. Inhibition of VEGF signalling through the use of antibodies or VEGF antagonists has demonstrated potent antitumour activity in the mRCC setting [35]. To date, nine targeted therapies have been approved by regulatory authorities in the United States and Europe, which have revolutionised the treatment of mRCC and largely contributed to what can be called the chronic care of this disease. As an example, in an unselected “real-life” cohort of 224 metastatic patients, the median OS for patients with a good prognosis, according to the Heng prognostic score [36], was 32 months [34]. This allowed expansion of the number of treatment options and sequences in this setting. Moreover, new generation immunotherapy has recently been approved by the FDA for a first-line setting [37].

From the patient’s perspective, it is essential that this improvement in the duration of survival is not at the cost of high toxicity; therefore, improvement of TKI tolerance has become a major topic of research in the mRCC field. For instance, the PISCES study evaluated patient preference of sunitinib or pazopanib [5]. Some trials have evaluated alternative administration schedules of sunitinib to improve its tolerability [38, 39]. In daily clinical care, the management of side effects related to TKI is an important part of mRCC patient care to enhance treatment compliance. A German group highlighted the fact that the benefit of these drugs may differ in routine practice as compared with patients included in clinical trials [40]. In parallel, there is increasing evidence that PRO in routine care may help in the management of sides effects [15, 16].

Several studies have provided evidence that the regular use of PROs, including HRQoL, improves communication between the patient and physician, in addition to HRQoL scores and survival [14]; however, these studies often took place in expert centres. The QUANARIE study will provide an opportunity to evaluate whether routine HRQoL monitoring is feasible outside expert centres*.* Furthermore, most of these trials have focussed on the management of side effects with PROs that only evaluate the occurrence of adverse events and their severity. In the QUANARIE study, the evaluation of HRQoL with the EORTC QLQ-C30 allows a multidimensional evaluation of the patient’s point of view, using functional and symptom scales. While EORTC QLQ-C30 is the most frequently used questionnaire in routine PRO, it is not the most frequent tool used in mRCC RCTs [21]; however, the items evaluated by the EORTC QLQ-C-030 and the National Comprehensive Cancer Network - Functional Assessment of Cancer Therapy-Kidney Symptom Index 19 (NCCN-FACT FKSI-19) are relatively similar [41], with both exploring symptoms such as asthenia, pain, nausea, diarrhea, and dyspnea, in addition to “function and well-being”. Nevertheless, while FKSI questionnaires are the most used in mRCC RCTs, they do not cover most symptoms related to TKI.

In the COMPARZ trials, a specific questionnaire, the Hand-Foot and Mucositis Symptom and Impact Questionnaire (HAMSIQ) was used in addition to the FKSI 19 questionnaire for the assessment of mouth/throat, hand/foot soreness symptoms, and subsequent limitations in patients receiving pazopanib or sunitinib for mRCC [27, 42].

Since the HAMSIQ questionnaire is not freely available, we used the EORTC Items Library to create new questionnaires based on the database of items used in fully and partially validated EORTC Quality of Life questionnaires. We added supplementary items to the QLQ C30 questionnaire that target the most frequent adverse events reported in sunitinib and pazopanib trials.

The integration of HRQoL assessment into daily clinical care faces multiple barriers such as material and IT limitations and implementation of an intervention that may increase the workload of already busy physicians or a training physician who is not familiar with interpreting HRQoL measures [23, 43–46]. The QUANARIE trial is part of a larger project led by the Methodological and Quality of Life Unit in Oncology (UMQVC) with the aim of integrating HRQoL monitoring as a complementary tool into daily clinical practice. Two other studies are currently recruiting patients: the GYNEQOL-Pilot [NCT02864797] and the QOLIBRY trial [NCT02844608]. To date, more than 360 patients treated for different types of cancer (gynecological, colorectal, lung, breast, and kidney) with different types of treatment (chemotherapy, TKI, and immunotherapy) have been included in these three clinical trials. The results of the QUANARIE study will demonstrate whether REMOQOL is feasible on a large scale and whether patients are receptive to this new practice. This study will also show how real-time multidimensional evaluation of patient perception can help physicians in their daily practice and how they can use it in conjunction with other clinical information to manage patient care.

## Abbreviations

CHES: Computer-Based Health Evaluation System software
COPD: chronic obstructive pulmonary disease
EORTC: European Organisation of Research and Treatment of Cancer
ePRO: electronic patient-reported outcome
EQ-5D: European Quality of Life – 5 Dimensions Questionnaire
ESD: Evaluation Software Development
FA: Fatigue
FDA: US Food and Drug Administration
HRQoL: Health-Related Quality of Life
ORR: Overall response rate
OS: Overall survival
PF: Physical Functioning
PFS: Progression-free survival
PRO: Patient-reported outcome
QL: Global Quality of Life
QLQ-C30: Quality of Life Core Questionnaire
RCC: Renal cell carcinoma
REMOQOL: Routine Electronic Monitoring of HRQoL
SmPC: Summary of product characteristics
TKI: Tyrosine kinase inhibitors
TTD: Time to HRQoL deterioration
TTP: Time to progression
VEGF: Vascular endothelial growth factor
